## Abstract

**Background:**

The presence of bone metastases has excluded participation of prostate cancer patients in exercise intervention studies to date and is also a relative contraindication to supervised exercise in the community setting because of concerns of fragility fracture. However, this group of patients often have developed significant muscle atrophy and functional impairments from prior and continuing androgen deprivation that is exacerbated by subsequent and more intensive interventions such as chemotherapy. The aim of this study is to determine the efficacy and safety of a modular multi-modal exercise program in prostate cancer patients with bone metastases.

**Methods/Design:**

Multi-site randomized controlled trial in Western Australia and New South Wales to examine the efficacy and safety of a modular multi-modal physical exercise program in 90 prostate cancer survivors with bone metastases. Participants will be randomized to (1) modular multi-modal exercise intervention group or (2) usual medical care group. The modular multi-modal exercise group will receive a 3-month supervised exercise program based on bone lesion location/extent. Measurements for primary and secondary endpoints will take place at baseline, 3 months (end of the intervention) and 6 months follow-up.

**Discussion:**

Delaying or preventing skeletal complication and improving physical function for men with bone metastases would provide clinically meaningful benefits to patients. However, exercise programs must be designed and executed with careful consideration of the skeletal complications associated with bone metastatic disease and cumulative toxicities from androgen deprivation such as osteoporosis and increased risk of fractures. The results from this study will form the basis for the development of a specific exercise prescription in this patient group in order to alleviate disease burden, counteract the adverse treatment related side-effects and enhance quality of life.

**Trial Registration:**

ACTRN: ACTRN12611001158954

## Background

Metastases to bone occurs in approximately 80% of men with advanced prostate cancer [1] and the majority of these patients are at risk of developing pathological fractures, hypercalcemia, bone marrow suppression and nerve compressions or spinal cord compressions that result in significant morbidity, limited function and decreased quality of life [2-4]. The clinical course of metastatic bone disease in prostate cancer survivors is relatively long, with a 5-year survival rate of approximately 30% [5]. Prostate cancer causes predominately sclerotic lesions and commonly metastasize to the pelvis and axial skeleton [6]. Therefore, patients with bone metastases experience considerable morbidity resulting from skeletal complications and fatigue secondary to chemotherapy for those with castrate-resistance prostate cancer [3,7]. Delaying or preventing skeletal complication, improving physical function and increasing levels of physical activity in prostate cancer patients with bone metastases can provide clinically meaningful benefits to patients.

Long-term androgen deprivation therapy (ADT) remains the first-line treatment for advanced metastatic prostate cancer, however it acts by inducing severe hypogonadism causing a number of cumulative adverse effects [8,9]. Some of these physical side effects include reduction of bone and muscle mass, increased fat mass and loss of neuromuscular strength [8,10]. We have shown that a 9-month exposure to ADT led to significant reductions in hip (1.5%), spine (3.9%), whole body (2.4%) and upper limb (1.3%) bone mineral density (BMD) [11]. We have also reported that men on ADT had significantly reduced upper- and lower-body muscle strength and impaired overall functional performance and balance compared to healthy aged-matched controls [12]. Notably, ADT has been associated with increased fracture risks and more importantly this risk increases with the number of doses of gonadotropin-releasing hormone agonist administrated [8]. These observations raise a major concern for men receiving long-term ADT for advanced prostate cancer, with reduced muscle strength placing prostate cancer patients at higher risk of falling particularly when combined with ADT induced reductions in bone strength, all of the sequelae of falls and fracture. This is a major concern as fractures cause significant morbidity and mortality in men [13] and has been correlated with decreased survival in prostate cancer patients with bone metastases [14].

Apart from previous ADT, men with bone metastases and castrate-resistant prostate cancer would commonly receive chemotherapy given the results of initial phase III trials indicating modest survival benefit for those with symptomatic disease [15,16]. A number of well-established adverse effects including nausea and severe fatigue are associated with chemotherapy [15]. Therefore, prostate cancer survivors with bone metastases suffer not only from the treatment-related side effects common to survivors with localised disease, but also from significant physical [17] and psychological [18,19] issues associated with bone metastatic disease and its treatment.

Clinical trials investigating the efficacy of exercise in prostate cancer survivors including our recent randomized controlled trial excluded those who had bone metastases [20-24], or bone lesions deemed 'unstable'[25] due to the potential increased risk of skeletal fractures. Nevertheless, recent guidelines on Exercise for Cancer Survivors by the American College of Sports Medicine [26] suggest that cancer survivors including those with bone metastases should "avoid inactivity" given the potential benefits of physical activity even for this group of cancer patients with advanced disease. However, it remains to be determined if exercise can be tolerated by patients with bone metastases given the absence of clinical data on exercise feasibility and efficacy in patients with bone metastases. This situation is highly detrimental since patients with bone metastases are reducing their physical activity levels for fear of bone fracture and clinicians are reluctant to refer patients with bone metastases for physical exercise programs. Such a strategy can only result in greater fatigue, reduced function and further declining muscle and skeletal integrity, greater risk of other chronic disease and reduced quality of life [3,4]. This project is unique as it tests the implementation of a modular multi-modal exercise program (M3EP) taking into consideration location/extent of bone metastases lesions as a strategy to maintain or enhance physical function in this group of patients with advanced prostate cancer. Further, the outcomes from this trial may provide novel data that could be translated to other cancer patients with bone metastases. This is the first trial to our knowledge which is specifically designed to address the potential beneficial effects of exercise in cancer patients with bone metastases.

## Methods/Design

This is a two-armed prospective randomized controlled trial that will examine the efficacy and safety of a modular multi-modal physical exercise program in prostate cancer survivors with bone metastases. The trial will be a multisite study with clinical sites in Western Australia and New South Wales. Participants randomly assigned to the M3EP exercise intervention group will receive a 3-month supervised exercise intervention program (based on bone lesion location/extent) (Table 1). Participants in the usual medical care group will be asked not to change their baseline levels of physical activity and will be offered the same exercise program after the 3-month control period if the intervention is deemed to be feasible and efficacious.

**Table 1 T1:** Summary of study design

Months	0			3			6
**Exercise **(M3EP)		Intervention (n = 45)			Follow-up from 3-6 month		

**Usual Medical Care**		Usual Care (n = 45)			**Usual Medical Care **to receive same intervention (M3EP) from 3-6 month		

### Recruitment

Subjects will be recruited by invitation of their specialist (radiation oncologist/urologists). Those entering the study will undertake a series of familiarisation sessions and baseline measurements prior to randomisation.

### Randomisation

Patients will be randomly allocated in a ratio of 1:1 to the two study arms for the experimental M3EP exercise intervention or usual medical care groups, subject to maintaining approximate balance regarding stratification for current chemotherapy (yes/no). A research methods consultant with no patient contact will be responsible for randomisation. The exercise physiologists and other researchers conducting the study measures will be blinded to a given participant's group allocation. The exercise intervention will be provided by exercise physiologists not in the research team or performing the tests.

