### Calculation of sample size

Data from our research team in prostate cancer patients indicates that the standard deviation (SD) for change in our primary outcome which is the physical function subscale of the Medical Outcomes Study Short-Form 36 (SF-36) equates to ~12 points following a 3-month intervention. Given the health status of men in the proposed study we anticipate that our 3-month exercise regimen will result in an increase of ~5 points in the physical function subscale of the SF-36 whereas the usual medical care group will result in an overall loss of ~3 points over 3 months. Therefore, we anticipate a difference between the exercise and usual medical care groups of ~8 points in change of the physical function subscale from baseline to 3 months. A priori, 36 subjects per group will be required to achieve 80% power at an alpha level of 0.05 (two-tailed), and to demonstrate a difference between groups at the end of the 3-month intervention. Therefore, to adequately ensure that we have sufficient subject numbers at the end of the intervention (accounting for a drop-out rate of ~20%), 90 subjects will be randomized in a ratio of 1:1 to exercise and usual medical care groups, respectively.

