#### Exercise intervention

The modular multi-modal physical exercise intervention program (M3EP) will comprise resistance, aerobic and flexibility exercises undertaken 3 times per week in an exercise clinic setting supervised by an exercise physiologist. Exercise training sessions will take approximately 60 min (this includes the warm-up and cool-down periods) and will be conducted in the Exercise Clinics at Edith Cowan University in Perth, and at the University of Newcastle's Central Coast campus in Ourimbah. The programme will include 6 exercises that target the major trunk, upper and lower body muscle groups, which we have used in a number of previous studies [21-23,27,43-46] including men on ADT. There will be a modular component for the resistance exercise prescription based on location/extent of bone metastases (Table 2). To ensure the progressive nature of the training program, subjects will be encouraged to work past the specific repetition maximums (RMs) prescribed. The resistance will be increased by 5-10% increment for the next set/training session if subjects are able to perform more repetitions than the RMs specified during a set. Moderate intensity and volume of resistance exercise will range from 10 to 12-RM (e.g. the maximal weight that can be lifted 10 to 12 times) using 3 sets per exercise. This program differs considerably from those commonly prescribed for survivors with localised prostate cancer. Specifically, the M3EP is designed to minimise compressive and shear loads on affected skeletal sites to account for the reduced load bearing capabilities of bone due to metastatic disease in specific regions. Such loading is considerably below the forces exerted on the skeleton during tasks of daily living such as descending stairs or stepping down from a height and will be similar to that of walking. All exercises will be performed at a set cadence of 2 s for both eccentric and concentric phases further minimizing peak forces transmitted to the skeleton. Aerobic exercise component of the M3EP will also be based on location/extent of bone metastases with those with pelvis, axial skeleton (lumbar), proximal femur and all regions bone metastatic disease undergoing non-weight bearing activities (Table 2). The aerobic component will include 20-30 min of cardiovascular exercise using various modes such as walking on a treadmill, cycling or rowing a stationary ergometer, or exercising on a cross training machine based on disease extent (Table 2). Target intensity will be 60%-85% estimated maximum heart rate (220 - age) with individual heart rate monitors (Polar Electro Oy, Finland) provided for each participant. The flexibility component of the M3EP will involve static stretching of all the joint ranges of motion considered important for function. Those with axial skeleton and all regions bone metastases will be excluded from undertaking spine flexion/extension/rotation (Table 2). The protocol will involve 2-4 sets per muscle group at 30-60 s per set as previously proposed [47]. All M3EP sessions will be conducted in small groups of up to 8 participants under direct supervision to ensure correct technique and minimal risk of injury. Each session will commence with a 10-minute warm-up comprising low-level aerobic activities such as treadmill walking and stationary cycling as determined by bone metastases site, as well as stretching and conclude with a 5-minute cool-down period of stretching activities. The M3EP will be designed to provide adequate stimulus to the cardiorespiratory, skeletal and neuromuscular systems while maximizing compliance and retention. All participants will be asked to maintain customary physical activity and dietary patterns over the intervention period (apart from the programmed exercise). Dietary intake will be assessed at baseline, 3 and 6 months using 3-day record. During the course of the study, participants will be required to maintain an activity log and record their recreational physical activities.

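### Randomisation balances on current chemotherapy only, although the trial recruits and exercises men at two distant sites, so avoidable chance imbalance by site remains

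*Protocol article*

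**What the plan says.** All references are to the protocol article.

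- **Sites.** Methods/Design: "The trial will be a multisite study with clinical sites in Western Australia and New South Wales". The Subjects section has attending specialists inviting men in Perth and in the Central Coast region. The Exercise intervention section has sessions "conducted in the Exercise Clinics at Edith Cowan University in Perth" and at a second university clinic in Ourimbah.
- **Allocation.** Randomisation: 1:1 to the two arms, "subject to maintaining approximate balance regarding stratification for current chemotherapy (yes/no"). No other factor is listed.
- **Delivery.** Exercise intervention: all sessions run in "small groups of up to 8 participants under direct supervision". In Table 1 the usual-care arm receives the programme only from month 3, after the primary comparison.
- **Sample size.** Calculation of sample size: "36 subjects per group will be required to achieve 80% power at an alpha level of 0.05 (two-tailed"), raised to 45 per arm for dropout. The calculation has no allowance for site or for group delivery.
- **Analysis.** Statistical analysis: t tests, correlation and regression, and a group-by-time repeated measures ANOVA, or ANCOVA where suitable, under intention to treat. No covariates are named and none are ruled out.

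**The concern.** In a two-site trial, site is the obvious second balancing factor. Each site has its own referring specialists and its own exercise clinic, so case mix and delivery could differ between them. The article does list its balancing factors, and site is not among them. This matters more for the allocation than it would for the analysis: a later analysis plan can add a covariate, but it cannot change how men were allocated.

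What is at stake is precision. If site is related to change in physical function and falls unevenly between the arms, part of the site difference enters the unadjusted treatment difference as chance error.

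A second, weaker question comes from the same design. Men in the exercise arm train under shared supervision and controls do not. If the same men train together throughout, their outcomes may be correlated in that arm only, and an analysis that treats all men as independent would then understate the standard error.

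**Working it through.** **1. The plan's own figure.** Inputs from Calculation of sample size: an SD of change that "equates to ~12 points following a 3-month intervention"; "we anticipate a difference between the exercise and usual medical care groups of ~8 points in change of the physical function subscale"; two-sided alpha 0.05; power 80%; and "accounting for a drop-out rate of ~20%), 90 subjects will be randomized in a ratio of 1:1".

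- n per arm = 2 × (1.960 + 0.842)² × 12² / 8² = 35.3, so 36. This reproduces.
- 36 / 0.80 = 45 per arm, 90 in total. This reproduces.
- Power at 36 per arm is 80.7% by the normal approximation and 79.7% by the exact t calculation, so there is no slack.
- Planned standard error of the difference = 12 × √(2/36) = 2.83 points.

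**2. Chance of site imbalance.** The article gives no site split, so three are assumed. With 45 men in each arm and no balancing on site, the number from the smaller site in one arm is hypergeometric (90 men, K from the smaller site, 45 drawn).

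| Assumed split of 90 | Arms differ by at least 10 percentage points in site share | At least 20 points |
|---|---|---|
| 45 / 45 | 40% | 9% |
| 60 / 30 | 26% (18:12 or worse) | 4% (20:10 or worse) |
| 72 / 18 | 19% | 2% |

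**3. Effect on the estimate.** Shift = (difference in site share) × (site difference in mean change). For a 20:10 split and an assumed 5-point site difference: (20/45 − 10/45) × 5 = 1.1 points. That is 1.1 / 8 = 14% of the planned effect and 1.1 / 2.83 = 0.4 of the planned standard error.

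**4. Average gain from adjusting.** With a 60/30 split and a 5-point difference, site explains (1/3) × (2/3) × 5² = 5.6 of a variance of 144. The residual SD is √(144 − 5.6) = 11.8 instead of 12, a gain of about 2%.

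**5. Conditional check on training groups.** Assume fixed groups of size m in the exercise arm only. That arm's variance is multiplied by DE = 1 + (m − 1) × ICC, and the standard error by √((DE + 1)/2). Type I error of an analysis that ignores this is 2 × [1 − Φ(1.96 / SE factor)]. Power is by the normal approximation with 36 evaluable men per arm. The ICC and the fixed membership are assumptions.

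| m | ICC | DE | SE factor | Type I error | Power |
|---|---|---|---|---|---|
| 4 | 0.01 | 1.03 | 1.007 | 5.2% | 80.2% |
| 4 | 0.05 | 1.15 | 1.037 | 5.9% | 77.9% |
| 4 | 0.10 | 1.30 | 1.072 | 6.8% | 75.1% |
| 8 | 0.01 | 1.07 | 1.017 | 5.4% | 79.4% |
| 8 | 0.05 | 1.35 | 1.084 | 7.1% | 74.2% |
| 8 | 0.10 | 1.70 | 1.162 | 9.2% | 68.2% |

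With fully mixed attendance (ICC 0) nothing changes.

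**The case against.** The strongest reply is that this is a matter of efficiency and not of validity. Randomisation makes site imbalance a chance event, and the unadjusted standard error already allows for it on average. A shift of 0.4 standard errors needs both an assumed 5-point site difference and a split with about a 4% probability, and the average gain from adjusting is near 2%. All of this stands, and it sets the weight of the point. It does not remove the point, because the remedy costs almost nothing.

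A reader might also infer stronger things that the document does not support:

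- **That site and training group are left out of the analysis.** The article plans ANCOVA and regression without naming covariates. An article commonly leaves the covariate list and any random effects to the full protocol or analysis plan, which is not shown.
- **That training group should have been a balancing factor.** Groups form after allocation and in one arm only, so this is not possible.
- **That the standard errors are too small.** This needs stable groups and a non-zero ICC. The article gives a ceiling on group size per session; it does not say that the same men stay together. Prescriptions are individual, by metastasis site (Table 2), and the primary outcome is a self-report score.
- **That patients or testing are known to differ by site.** No section says so, and one set of tests is specified for the whole trial.
- **That imbalance is more likely than shown here.** A binomial model for 30 men gives 36% for 18:12 or worse and 10% for 20:10 or worse, but it lets the arm sizes vary. The plan has 45 per arm, which gives 26% and 4%.

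**Conclusion.** The point holds as a minor design improvement. The stated allocation rule balances on chemotherapy alone in a trial with two distant recruiting and delivery sites, so a chance imbalance by site is left open that could have been closed. The cost is some precision, with no systematic bias. With an assumed 60/30 site split and 45 men per arm, an imbalance of 18:12 or worse occurs in about one trial in four. Even the rarer 20:10 split, with an assumed 5-point site difference, moves the estimate by only about 1.1 points against a planned effect of 8.

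The clustering question is secondary and conditional. The arithmetic is sound, but the upper end (type I error 9.2%, power 68.2%) needs fixed membership, the maximum group size and the highest assumed ICC together, and the article documents none of these as holding. It supports a sensitivity analysis, not a change to the primary analysis or the sample size.

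**What to change.** - **Allocation.** Add site (Perth / Central Coast) as a second balancing factor beside current chemotherapy.
- **Primary model.** Include both factors as covariates, and name them in advance.
- **Training groups.** State whether exercise groups have fixed membership. If they do, record each man's group and run one sensitivity analysis with a random effect for group in the exercise arm only.

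**Cost.** Four strata for 90 men, which is workable, and one or two degrees of freedom in the model. The sensitivity analysis needs one extra recorded variable. With 45 men in groups of up to 8 there would be only about six groups (45 / 8 = 5.6), so its variance estimate will be imprecise and should be read as supportive only.

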### Subjects

Ninety men (45 subjects per arm) with prostate cancer and established bone metastases with no regular exercise (undertaking structured aerobic or resistance training two or more times per week) within the past 3 months will be recruited through invitation by their attending specialist in Perth, Western Australia, and the Central Coast region of New South Wales. All participants will require physician consent. Exclusion criteria will include acute illness, significant bone pain, musculoskeletal or cardiovascular or neurological disorders that could inhibit or put them at risk from exercising. The protocol has been approved (ID: 7699 [name]) by the Edith Cowan University Human Research Ethics Committee and all participants will provide written informed consent.

### Calculation of sample size

Data from our research team in prostate cancer patients indicates that the standard deviation (SD) for change in our primary outcome which is the physical function subscale of the Medical Outcomes Study Short-Form 36 (SF-36) equates to ~12 points following a 3-month intervention. Given the health status of men in the proposed study we anticipate that our 3-month exercise regimen will result in an increase of ~5 points in the physical function subscale of the SF-36 whereas the usual medical care group will result in an overall loss of ~3 points over 3 months. Therefore, we anticipate a difference between the exercise and usual medical care groups of ~8 points in change of the physical function subscale from baseline to 3 months. A priori, 36 subjects per group will be required to achieve 80% power at an alpha level of 0.05 (two-tailed), and to demonstrate a difference between groups at the end of the 3-month intervention. Therefore, to adequately ensure that we have sufficient subject numbers at the end of the intervention (accounting for a drop-out rate of ~20%), 90 subjects will be randomized in a ratio of 1:1 to exercise and usual medical care groups, respectively.

